**Fig 1 pone.0274193.g001:**
[figure not shown]
SPIRIT 2013 schedule. SPIRIT schedule of enrollment, interventions and assessments timepoints along the study period (1 year maximum after the allocation).

**Fig 2 pone.0274193.g002:**
[figure not shown]
Study methods flow chart. 134 participants will be assessed for elegibility, allocating 67 in each arm (experimental and control groups). COT-MHABI protocol will be applied in experimental group and regular health care interventions in control group. For both groups, outcomes will be assessed over a one-year period at baseline, by the 6^th^ and 12^th^ month, when data collection is closed and analysis begins.

### Intervention

#### Experimental group: Community-based occupational therapy intervention in mental health for people with ABI

Participants in the experimental arm will receive the COT-MHABI protocol, carried out after they are discharged and returned to their communities. This protocol is composed of two main phases. In the first phase, an occupational assessment will be carried out. Based on the results obtained in the assessment, goals setting will take place.

The second phase of the COT-MHABI protocol corresponds to the intervention process. This process will be composed of several sessions divided in stages implemented through an occupation-based and occupation-focused intervention [44]. The structure of the intervention will be an adaptation from the MOHO Remotivation Process [18,23], which has as one of its main objectives the facilitation of occupational participation by people with severe volitional and motivational disorders [23]. The COT-MHABI protocol will follow the diagram shown in Fig 3.

**Fig 3 pone.0274193.g003:**
[figure not shown]
Outline of the COT-MHABI intervention process. The intervention will begin with an initial comprehensive assessment during the first session. The goals are agreed with the participant in the following sessions based on a specific assessment. Subsequently, between the 4th and the 16th session (on-site and telematics), the intervention will be implemented according to the goals and through the three-level process (Exploration, Competence and Achievement) based on the Model of Human Occupation.

Once a person agrees to participate in the study, an information sheet will be handed out, and the consent forms will be signed. The principal investigator, an occupational therapist with 15 years of experience, will carry out the intervention and the evaluations at the experimental group.

This intervention will have a duration of one year. During this time, a maximum of 12 on-site sessions and 4 synchronous telematic sessions in video-call format are foreseen. The on-site sessions, which will take place in a home and/or community environment, will last between 60 and 90 minutes, depending on the objectives set, and the telematic sessions will last approximately 45 minutes. In an exceptional case in which it is not possible to carry out the session in person or by video-call, it will be carried out by a telephone call. Likewise, both telephonic and asynchronous communication (e-mail or text messages) will be considered for possible exchanges of information or contingencies, without these communications constituting an intervention session per se.

During the COT-MHABI assessment phase, at the first session, an initial comprehensive assessment will be carried out, where the occupational therapist will collect information regarding the occupational history, i.e., meaningful activities for the person and their impact on the life narrative and about current occupational participation, i.e., the occupations that the person is effectively performing at the time of the assessment. During the second session, a specific assessment will be carried out, where a detailed analysis of relevant areas and facilitators/hinderers of occupational participation will be performed together with an exploration of significant roles and the person’s expectations about them. Based on this information and the information gathered in the first session, the objectives will be established with the person’s agreement.

In order to achieve the objectives, the COT-MHABI intervention phase will be carried out during the rest of the process. This will be defined on the basis of three sequential and interrelated levels: (a) Occupational Exploration, (b) Occupational Competence, and (c) Occupational Achievement. Each level corresponds to a series of stages composed, in turn, of intervention strategies. A schematic summary of the composition of these levels can be seen in Table 1, while the complete list of strategies and goals corresponding to each level appears in the S1 Appendix
*at Supporting Information* section of this protocol.

**Table 1 pone.0274193.t001:** Composition of the intervention process levels.

Levels	Stages	Stage goals	Intervention strategy example
Occupational exploration	Validation	Enable access to initial experiences of capability through meaningful activity in a safe environment.	Accompaniment and support in initial experiences of capacity in acceptable and meaningful occupational forms.
	Willingness to explore	Favour an optimal basal state for allowing environmental exploration.	Provide strategies for promoting autonomy in managing difficulties related to mental well-being and post-ABI deficits.
	Election	Enable the person to increase his or her sense of capability during the exploration and choice of new habits and roles.	Facilitate exploration of new volitional opportunities according to the social and community environment.
	Effectiveness	Promote continued development of the person’s sense of efficacy through exploration and preliminary participation in meaningful habits and roles.	Facilitate accessibility to occupational forms and tasks appropriate to the routines and chosen roles.
Occupational Competence	Internalisation of a sense of effectiveness	Foster self-analysis of capacity and effectiveness in performance, planning challenges and objectives, in congruence with aspects of habituation (habits and roles) and the physical and social environment. Promote the acquisition of management strategies to face the difficulties present in his/her occupational performance.	Provide counselling to the family and social environment to optimise the ability to detect and assess effectiveness milestones and their importance within the rehabilitation process.
	Occupational narrative building	Facilitate the realisation of occupational actions and roles that develop and improve affected skills (motor, processing, communication and interaction). Facilitate registration of the new occupational narrative of continuity (role project).	Facilitating the continuity of the process of inscribing a sense of effectiveness through positive feedback.
OccupationalAchievement	Achievement	Facilitate internalisation of habits and execution of meaningful roles and consolidation of occupational actions that improve occupational performance. Optimise the occupational balance of the person and family environment in relation to the new occupations achieved. Provide information and support for continued performance in the post-intervention phase.	Provide preventive strategies for barriers to achievement in occupational participation.

Thus, the general proposal of the intervention process will be to carry out a progressive path that enables the person to experience how to (i) explore new occupations through the development of awareness of one’s own capacity in a safe environment, (ii) integrate these new learnings into habits congruent with the demands of the roles and the physical and social environment, experiencing an increase in personal effectiveness, and (iii) carry out an effective increase in occupational participation that has a permanent impact on occupational identity, in congruence with the pattern of life desired by the person. These strategies, proposals, and actions will be aimed at seeking personal autonomy through the use of meaningful activity, adaptation to the physical environment, and optimisation of the relationship with the social and family environment [18,23].

The therapeutic intervention process will be complemented with counselling actions in relation to ABI and mental health for social and health care resources and, in general, for community agents involved in the planning of occupational participation of the person. Likewise, actions will be carried out to connect resources required by the intervention, always with the aim of facilitating an optimisation of occupational performance that fosters participation and occupational balance, both for the person and the family environment.

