### Data collection

Outcome variables will be assessed in both study groups at the beginning of the COT-MHABI protocol, 6 months after the start of the protocol, and after the end of the protocol (12 months) using the scales detailed in Table 2. The collection will be carried out by different researchers. To minimise potential discrepancies, one researcher will allways evaluate the same participant.

**Table 2 pone.0274193.t002:** Tests and variables used in the data analysis.

Test	Outcome variable definition	Scores and Domains	Reliability
*Main outcomes*			
WHOQoL-BREF	Quality of life	**Quality of life (Total score: Min 26-Max 130)** (Domains: general QoL, health status satisfaction, physical health, psychological health, social relationship and environment)	ICC = 0.87
COPM	Self-perceived occupational performance	**Performance change**: difference between measures in self-perceived occupational performance **(Total score: Min 0-Max 50)** **Satisfaction change**: difference between measures in occupational performance satisfaction **(Total score: Min 0-Max 50)**	r = 0.87–0.88
*Secondary Outcomes*			
SOD-EO	Satisfaction with daily occupation, occupational balance and activity level	**Satisfaction (Score: Min 13-Max 91)** Activity level (Score: Min 0-Max 13) Occupational Balance (Score: profile, no min or max) (Domains: productivity, leisure, home tasks and selfcare).	r = 0.84–0.92
RCv3	Satisfaction with performed roles	**Satisfaction (Score: Min 0.00-Max 1.00)** Number of performed roles (Score: Min 0-Max 10) Participation (Score: Min 0.00-Max 1.00) Desired Performance (Score: Min 0.00-Max 1.00)	r = 0.74–1.00
ACS	Perceived activity participation level	**Percentage of maintained activities after ABI (Total score: Min 0%-Max 100%)** (Domains: instrumental activities, low physical demand leisure activities, high physical demand leisure activities, social and educational activities)	r = 0.88–0.95
CIQ	Community integration and participation	**Community integration and participation (Total score: Min 0-Max 29)** (Domains: home integration, social integration and productivity)	r = 0.83–0.93
FIM	Functional Independence	**Functional Independence (Total score: Min 18-Max 126)** (Domains: motor and cognitive)	ICC = 0.85

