#### Main outcomes

*Quality of life*. This will be measured by the WHOQoL-BREF (World Health Organization Quality of Life-BREF, Spanish version) [45,46]. This is a generic self-administered questionnaire created by the Quality of Life Study Group of the World Health Organization (WHO). The instrument has 26 questions, two general questions on quality of life and satisfaction with health status, and 24 questions grouped into four areas: Physical Health, Psychological Health, Social Relationships and Environment. Higher scores indicate better perceived quality of life. A 5-point Likert-type response scale is used. The WHOQoL-BREF shows excellent reliability (ICC = 0.87) for the quality of life variable in ABI due to traumatic brain injury [47].

*Perceived occupational performance and satisfaction with performance*. This will be evaluated by COPM (Canadian Occupational Performance Measure, Spanish version) [23,48], which is a self-administered occupational therapy measure based on client-centred practice that helps to establish occupational needs. It assesses changes in self-perceived occupational performance and satisfaction with occupational performance following intervention. The COPM shows excellent reliability (r = 0.87–0.88) in stroke patients [49].

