*Community integration*. This will be measured from the results collected in the CIQ (Community Integration Questionnaire, Spanish version) [57]. It assesses the limitations in the performance of social roles and community interaction of people with ABI. It presents three main dimensions: domestic integration, social integration and productivity. The total score range is between 0–29 and most items have a range of 0–2. Higher values represent greater community integration and independence. The test-retest reliability of this scale is excellent for this population (r = 0.83–0.93) [57,58].

*Functional independence*. This will be valued from the FIM scale (Functional Independence Measure, Spanish version) [59,60]. The scale represents a uniform measurement system for disability based on the International Classification of Impairment, Disabilities and Handicaps. It assesses six functional areas (self-care, sphincter control, transfers, locomotion, communication and social cognition) within two domains (motor and cognitive). Each item is scored on a 7-point Likert-type scale. The items are performance-based rather than ability-based and are recorded in a hetero-administered manner. Reliability is excellent for the ABI population [60].

*Satisfaction with the intervention process*. This is a provider hospital’s internal questionnaire (Spanish version). This will be collected qualitatively and quantitatively by regular programme satisfaction questionnaires. In this case, there is one questionnaire for the person participating in the process and another one for the main referring family member, if any. Both questionnaires are composed of seven questions about the subjective perception of the results obtained after the intervention with a 7-point Likert-type response scale. In addition, there are 4 more questions that, with a scale of 1 to 10, aim to collect the opinion of the quality of the intervention. Finally, a section will be included where, in a qualitative manner, the person can express other comments not included in the previous questions.

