#### Data management

The data will be coded and stored by the research department of the patient provider, the Institut Guttmann Neurorehabilitation Hospital.

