### Limitations

Due to the technical feasibility of the programme, where the intervention is carried out, the clinical and social complexity of this patient profile, the lack of evidence on similar programmes and interventions, and the difficulties in finding a population in the setting that falls within the range of the inclusion and exclusion criteria, the presence of these issues that may interfere with the results and lead to bias should be highlighted.

The following have been identified as the main ones: (i) the inclusion of various aetiologies of ABI as a generalised concept, when the clinics presented by the patients may differ considerably [62]; (ii) the difficulty of knowing the influence of the different treatments that the patients in the control group may receive; (iii) the variability in the different conceptions of the construct "mental health" and its implications in the design of the protocol itself as well as in the practice on the quality of professional support that this population profile receives; (iv) due to the technical particularities of the research proposal, the therapist delivering the intervention and subsequently analysing a large part of the data is the same person, which may lead to biases in the results; (v) the heterogeneity in terms of the range of time after ABI in which the intervention takes place, as both groups have a wide range. This is because, at present, this is the first time that this type of support initiative is being provided in this region; so, patients are not screened according to the time of acquisition of the brain injury but by the importance of the current condition and their personal, occupational, social, and family issues.

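### The treating therapist evaluates the experimental arm, so an assessor-related or courtesy shift that arises after baseline cannot be separated from the treatment effect, and the limitations do not disclose this

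*Protocol article*

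**What the plan says.** All references are to the protocol article.

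- **Intervention, Experimental group:** the principal investigator, an occupational therapist, "will carry out the intervention and the evaluations at the experimental group".
- **Data collection:** outcomes are taken in both groups at the start, 6 months and 12 months. "The collection will be carried out by different researchers", and, to limit discrepancies, "one researcher will allways evaluate the same participant". No control-group assessor is named and no masked assessment is described.
- **Main outcomes:** of the WHOQoL-BREF, "This is a generic self-administered questionnaire"; of the COPM, "which is a self-administered occupational therapy measure based on client-centred practice". Table 2 defines the COPM outcomes as differences between measurements.
- **Secondary outcomes:** FIM items "are recorded in a hetero-administered manner", and the ACS is worked through jointly with the patient.
- **Statistical analysis:** normally distributed variables go into a repeated measures ANOVA with three time points and two groups. Other variables are compared between groups by the Mann-Whitney test, with no baseline adjustment stated. The article does not say which ANOVA term decides effectiveness.
- **Limitations (iv):** "the therapist delivering the intervention and subsequently analysing a large part of the data is the same person", which is acknowledged as a possible source of bias.
- **Data management:** "The data will be coded and stored by the research department of the patient provider".

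**The concern.** The trial is non-randomised and open, and both main outcomes are subjective. If the person who treats a patient for a year also takes that patient's outcomes, two things may move the experimental arm without any real benefit. The rater may score more generously as treatment proceeds, or the patient may give kinder answers to someone known from up to 16 sessions. Controls have no such relationship.

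The fixed-researcher rule keeps the therapist in place at every visit of every experimental participant. If controls have other assessors, assessor is nested within arm and no later model can estimate the two effects separately. The analyst overlap is disclosed. The assessor overlap is not, so a reader of the results would not know to allow for it.

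**Working it through.** **1. Does evaluations mean outcome evaluations?** The Experimental group section uses assessment for the clinical work-up in sessions 1 and 2. Statistical analysis uses evaluation for the intermediate and final outcome time points, and Data collection uses the verb evaluate for outcome collection. The outcome reading is the natural one.

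**2. The plan's own sample size.** Inputs from Power analysis: d = 0.49, two-sided alpha 0.05, power 0.80. Normal approximation: n per arm = 2(1.960 + 0.842)² / 0.49² = 65.4, so 66. The t test (noncentral t) gives 66.35, so 67 per arm and 134 in total, with power 0.804. The stated 134 is reproduced.

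**3. How many evaluations are exposed.** The therapist makes 67 × 3 = 201 evaluations. The 67 at baseline precede treatment, so 67 × 2 = 134 could carry a shift caused by the treatment relationship.

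**4. What each kind of shift does.** Let δ be the shift in SD units in the experimental arm, with no true effect.

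| Shift at 0, 6, 12 months | 12-month minus baseline contrast | Three-visit mean (group main effect) |
|---|---|---|
| δ, δ, δ (stable offset) | δ − δ = 0 | δ |
| 0, δ, δ (after baseline) | δ − 0 = δ | 2δ/3 |

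A stable offset therefore drops out of group-by-time and of COPM change. It stays in a group main effect and in a Mann-Whitney test on unadjusted scores.

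**5. Rejection rates with no true effect.** Simulated 3 × 2 repeated measures ANOVA, 67 per arm, 4,000 runs. The correlation between visits (0.7) and the shift sizes are assumptions; the article gives neither.

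| Shift | Group main effect | Group × time |
|---|---|---|
| none | 5.3% | 4.6% |
| 0.2 SD at all visits | 26% | 5.4% |
| 0.3 SD at all visits | 48% | 4.7% |
| 0.2 SD after baseline | 14% | 32% |
| 0.3 SD after baseline | 25% | 64% |

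Analytic check of group × time for a shift after baseline: noncentrality λ = (67/2)(2/3)δ² / (1 − 0.7) = 74.4δ², that is 2.98 and 6.70. The noncentral F on 2 and 264 degrees of freedom then gives 32% and 63%, in agreement.

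**6. Range over the assumed correlation r.** Two-sample t test on the 12-month change, SD of change = √(2(1 − r)), noncentrality = δ / (SD of change × √(2/67)):

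| r | δ = 0.1 | δ = 0.2 | δ = 0.3 |
|---|---|---|---|
| 0.5 | 9% | 21% | 41% |
| 0.7 | 12% | 32% | 61% |
| 0.87 | 20% | 62% | 92% |

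The top value of r is the WHOQoL-BREF reliability in Table 2, used only as an upper end. As shares of the design effect, the shifts are 0.1/0.49 = 20%, 0.2/0.49 = 41% and 0.3/0.49 = 61%.

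**The case against.** The strongest case on the other side has four parts.

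- **Complete separation is not stated.** A reader might infer that assessor and arm are fully confounded. The article does not say that the therapist evaluates no controls, and it leaves the control assessor unnamed. Separation is the natural reading of the two sections together, but it remains an inference.
- **The fixed-researcher rule also protects.** A reader might infer that any rating difference becomes treatment effect. That is not so: a stable difference between assessors leaves group-by-time at about 5%. The protection does not extend to a shift that develops during treatment, to a group main effect, or to unadjusted Mann-Whitney comparisons.
- **Both main outcomes are described as self-administered.** This stands. Direct rater shift applies mainly to FIM and ACS, which are secondary. For WHOQoL-BREF and COPM the remaining risk is courtesy in answers given to one's own therapist. That plausibly favours the intervention, but the documents establish neither its direction nor its size.
- **Some safeguards exist.** The referring department is kept out of allocation, intervention, collection and analysis (Recruitment methods). The hospital's research department may audit and takes no part in collection or intervention (Ethics). Limitation (iv) discloses the analyst overlap. None of these changes who evaluates the experimental arm.

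**Conclusion.** The point holds in limited form and should be fixed. As written, the treating therapist evaluates the experimental arm, others apparently evaluate controls, and a shift arising after baseline cannot be told apart from benefit by any analysis. The limitations section is silent on this.

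The possible size is material. With no true effect, an assumed shift of 0.2 or 0.3 SD after baseline gives a significant group-by-time test about 32% or 64% of the time at a correlation of 0.7. On the 12-month change, the range over correlations of 0.5 to 0.87 is 21% to 62% for 0.2 SD and 41% to 92% for 0.3 SD. These figures show sensitivity and do not estimate the bias: shift sizes and correlations are assumptions. It would go too far to say that both main outcomes are biased in favour of the intervention, or that every assessor difference turns into effect.

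**What to change.** 1. At all visits, WHOQoL-BREF and the COPM ratings are completed without the therapist present and returned to the research department, which already codes the data.
2. The researchers who already collect data are shared across both arms. The same non-treating researcher makes the baseline, 6- and 12-month outcome evaluations of a given participant, at least for FIM and ACS. All three visits must be covered: moving only the follow-up visits would change the assessor after baseline in the experimental arm alone. The therapist keeps the clinical assessment in sessions 1 and 2.
3. A team member other than the therapist runs the main analysis on a file with arms labelled A and B. Labels alone would mask little from an analyst who treated every experimental participant.
4. Any assessor overlap that remains is added to limitation (iv), and the control-group assessor is named.

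Sample size, instruments, visits and the one-researcher-per-participant rule stay as they are. Items 1, 3 and 4 cost little. Item 2 needs coordination and shifts workload among existing researchers. The article does not give their number or capacity, which is why FIM and ACS are set as the minimum. Under item 2 the evaluator is no longer the patient's usual contact, and some baseline work may run alongside the therapist's own assessment.
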